#### Intervention group – open access telePRO

In open access, contact to the outpatient clinic is initiated by the patient by filling in a PRO questionnaire. The same questionnaire is used as in standard telePRO, but the patient decides when to respond. The patients can access a PRO overview, “My Epilepsy”, customised for patient use via a secure login at the Danish national health website “Sundhed.dk”. The clinicians handle questionnaires in the same way as in standard telePRO.

#### The open access website “My Epilepsy”: design and features

A prototype website, “My Epilepsy”, was developed to collect PRO in patient-initiated outpatient follow-up. The website was linked with the Danish National Health Website ‘Sundhed.dk’. The website, “My Epilepsy”, was customised for patient use and designed to allow patients to: a) answer a PRO questionnaire to get in contact with the clinic, b) view their personal PRO data (previously questionnaire responses), c) view information about the epilepsy questionnaire and specific questions, and d) have access to contact information to the epilepsy outpatient clinic. A research team that included, outpatients with epilepsy and experts in telePRO, patient involvement, software technology, clinical epilepsy, provided inputs to design the prototype website. The research team developed the initial website specifications, constructed the website, and elicited feedback from epilepsy outpatients (*n* = 6), using cognitive interviewing techniques to study the manner in which the patients understood and responded to the website. The interface is shown in Fig. 2. Patients emphasised the importance of a user-friendly interface with clear and concise information. Patients were interested in tracking change over time and in using the website because it gave them the potential to communicate with their clinicians at a time decided by themselves. They found it conceivable that access to their previous questionnaires could give them a better understanding of their chronic disease. Finally, they pointed out the need for a telephone number if they required immediate contact. Patients had few problems assessing and using the site.

**Fig. 2 Fig2:**
[figure not shown]
The open access telePRO website “My Epilepsy”. Note: Labels were translated from Danish

The website consists of four core elements:Answer questionnaire: Here, patients can answer the epilepsy questionnaire when they need to get in contact with the clinic. The questionnaire is the same as in standard telePRO. When the patient has completed the questionnaire, the response is automatically sent as a red request to the PRO alert list at the epilepsy clinic. The clinician assesses the response and contacts the patient as soon as possible. The clinic has reserved appointments in their booking system to ensure that patients get a quick appointment. As a “safety net”, patients have to answer the questionnaire before twice the fixed interval has elapsed. For example, if the patient is referred with a 12-month interval, the patient has to respond within two years. If not, the patient is automatically sent a questionnaire, given a red status, and is contacted by a clinician.Previous answers: In this element, all of the patient’s previous questionnaire responses are available. Patients have access to a PRO overview interface and specific and detailed questionnaire responses in the same manner as the clinicians. The overview interface is shown in Fig. 3. It is customised to monitor selected PRO data and to illustrate changes in health status over time. Colour codes indicate the severity of the symptoms reported by the patient. A red or orange bar indicates a self-reported problem, a yellow bar some problem, and green bar indicates no problems.

**Fig. 3 Fig3:**
[figure not shown]
PRO response overview customised to outpatients with epilepsy. A red or orange bar indicates a self reported problem, a yellow bar some problem, and green bar indicates no problems. Note: Labels were translated from DanishInfo: This element includes information about the open access approach including detailed information about the purpose and how to use the website. In addition, there is information about the questionnaire and why it is important to gather information about the included aspects, e.g., seizures, alcohol, pregnancy, sexuality, etc. The information provided is compiled by clinicians from the epilepsy clinics at Aarhus University Hospital and is based on disease-specific guidelines and information from the Danish Epilepsy Association.Contact: Patients are asked to contact the epilepsy clinic by telephone in the event of a pressing need of attention. This element contains contact information (telephone number, email and mail addresses) to the epilepsy clinic. The emergency service is always open for those in acute need for help, for example, if the patient gets a seizure.

### Randomisation

Pre-randomisation designs prevent change in behaviour in the control group because of disappointment about the allocation [19]. Eligible standard telePRO participants will be pre-randomised to standard telePRO follow-up (no change) or open access telePRO follow-up. Control as well as intervention participants receive the baseline questionnaire together with the fixed PRO questionnaire. The clinicians respond to the fixed PROs as usual and will not have access to the baseline questionnaire. Control participants will continue with fixed interval questionnaires and no change will be undertaken. Intervention participants will receive detailed information about the open access approach two weeks after a clinician’s response to the fixed PRO questionnaire. The study coordinator will forward written information to the included intervention participants. Individuals who not agree to participate will continue with standard telePRO follow-up. Due to the nature of the intervention neither patients nor clinicians can be blinded to allocation. The randomisation is performed with an algorithm developed as part of the WestChronic software [12]. The allocation ratio open access/standard is 0.55/0.45. This ratio was selected to account for an expected number of patients in the open access arm who do not wish to participate.

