### Sample size

Statistical power was estimated for the primary outcome number of contacts. Based on literature review [32] the number of consultations (n) and standard deviation (SD) was; *n* = 4.64, (SD = 2.38) in conventional follow-up and *n* = 4.12, (SD = 3.41) in open access follow-up. We expect at least a difference of one contact between the groups. Given a statistical power of 90%, *p*-value 0.05, and allocation ratio 0.8, we will need a sample size of 172 patients in the standard telePRO group and 214 patients in the open access telePRO group. To account for attrition and loss to follow-up, we will recruit a total of approximately 500 participants. For qualitative data, a purposeful sample of at least five participants from each group will be interviewed.

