### Analyses

Descriptive statistics will be used to describe differences in the baseline characteristics of participating patients in the two arms of the trial. Statistical analysis will be intention to treat, whereby all randomised participants will be included in the analysis according to their randomised allocation. The primary outcome, total *number of contacts* in the two arms*,* will be analysed using a sample t-test. If the distribution of data is skewed, we will use medians and nonparametric tests. For secondary outcomes, a chi-square test or logistic regression will be used for dichotomous outcome data and sample *t*-test or multiple linear regression analysis will be used for continuous outcome data. Non-parametric tests will be used if continuous data are not normally distributed. Demographics covariates (sex, age, education, marital status, and epilepsy diagnosis duration) will be included in the per- protocol analysis.

For qualitative data, ID will be employed as the overriding research approach. ID is an inductive research strategy in which constant comparative method with concurrent data collection and analysis is utilised to gain a deeper insight and understanding of human experiences within their natural context. The result is a comprehensive interpretation, potentially a *model of explanation* of the phenomenon under study, which can provide clinical practice with a research-based choice of action [31]. ID is considered appropriate in the present study because the approach is suited for exploration of specific clinical issues, in this case how patients with epilepsy experience standard and open access telePRO follow-up.

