### Ethics

The risks to participants are considered to be minimal as all eligible participants are referred to standard telePRO follow-up by clinicians at the epilepsy clinic. As a “safety net” to ensure that no patients are lost in the open access arm, the patients have to answer the epilepsy questionnaire before twice the fixed interval has elapsed. If lack of response the patient is reallocated into standard telePRO with a red status and a clinician will contact the patient. Furthermore, all patients are informed to call the clinic in pressing need of attention.

The Danish Data Protection Agency has accepted the study. In addition, the Danish research ethics committee in Central Denmark Region was contacted and has stated that approval from the committee is not necessary for this present study. Therefore, written informed consent was not obtained from the participants. Prior to study participation patients in the intervention group receive written information about the study. Study participation is entirely voluntary and participants are informed they can withdraw from the study at any time without affecting future care. In the qualitative complementary PhD study, the participants gave written informed consent prior to enrolment, and the study was approved by the Danish Data Protection Agency.

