## Discussion

During the last decade, the use of PRO in clinical practice has become increasingly common, and to our knowledge, AmbuFlex is the first generic PRO system that uses PRO as the basis for outpatient follow-up [13]. The focus of this trial will be to evaluate the effect of a patient-initiated open access telePRO intervention compared to standard telePRO with respect to resource utilisation, quality of care, and the patient perspective. Ideally, we would have preferred to compare the two arms (standard and open access) with conventional follow-up with pre-booked outpatient visits to the clinic. However, this was not possible because the epilepsy clinics in Central Denmark Region have used standard telePRO follow-up since 2012. Thus, we will compare two rather similar outpatient follow-up activities, which will probably result in only small differences in effect between the groups. Evaluation of the effect must be done using reliable, valid, and clinically meaningful measures. This study includes outcome measures based on recommendations from clinical experts, researchers, and the literature [33].

Loss to follow-up is one of the main concerns in randomised controlled studies [34]. Loss to follow-up in this study is related to the open access group of patients since study participation in the open access arm is entirely voluntary, and participants can choose to continue with standard telePRO follow-up. Loss of statistical efficiency can be overcome by increased the number of participants in the study [19]. We have taken this into consideration and will include 10% more patients in the open access telePRO arm. In addition, we will recruit a larger number of participants than the minimum sample size calculation indicated.

Only web-responders will be included in the open access arm, and the results may therefore be generalizable only to this subgroup of epilepsy patients. These patients may differ with respect to education, age, and use of new technologies compared to the entire group of epilepsy patients. In another study in progress, the aim is to examine determinants for referral to telePRO follow-up. Data from this study can be used to compare the study population with the entire group of patients with epilepsy.

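### Patients who decline open access are planned for as replaceable losses, but under the stated intention-to-treat analysis they stay in the arm and dilute the effect, which the power statement does not allow for

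*Protocol article*

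**What the plan says.** **Randomisation.** Eligible patients are allocated before they are told about open access. Those who then decline stay on standard telePRO. The open access/standard ratio is 0.55/0.45, and the reason given is: "This ratio was selected to account for an expected number of patients in the open access arm who do not wish to participate".

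**Sample size.** The calculation uses a difference of one contact, SDs of 2.38 (conventional) and 3.41 (open access), 90% power, p-value 0.05 and an allocation ratio of 0.8. It gives 172 standard and 214 open access patients, 386 in all. Recruitment is raised to about 500 to cover attrition.

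**Discussion.** "Loss to follow-up in this study is related to the open access group of patients", because taking part in that arm is voluntary and patients may remain on standard telePRO. The loss of efficiency is to be met in two ways. One is the unequal arms: "We have taken this into consideration and will include 10% more patients in the open access telePRO arm". The other is a total above the calculated minimum.

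**Analyses and Primary outcome.** The analysis is by intention to treat: "all randomised participants will be included in the analysis according to their randomised allocation". The primary outcome, number of contacts, comes from a hospital register. A per-protocol analysis is also mentioned.

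**The concern.** Enlarging one arm replaces refusers only if refusers leave the analysis. Here they do not. Their contacts are in the register and the analysis keeps them where they were randomised, so they count as open access patients who received the control condition. What they cost is a smaller between-arm difference. Extra patients make up for that far less efficiently than they make up for missing data.

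Two things are at stake. First, the power of the primary comparison depends on a decline share that the article does not give, in a trial whose Discussion already expects only small differences between the arms. Second, the loss wording could lead someone at analysis to leave decliners out. Controls are never offered the choice, so that would compare acceptors with all controls and give up the protection of randomisation.

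**Working it through.** **Inputs.** From Sample size: δ = 1 contact, SDs 2.38 and 3.41, "Given a statistical power of 90"%, and "value 0.05, and allocation ratio 0.8" (standard to open access, so k = 1.25). From Randomisation: 0.55/0.45, which is 275/225 of 500. Sidedness is not stated. Two-sided 0.05 is assumed because it reproduces the stated size. Then z = 1.960 + 1.282 = 3.2415 and z² = 10.507.

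**Step 1: reproduce the stated size.** n(standard) = (SD_std² + SD_open²/k) × z²/δ².
- SDs as labelled: (5.664 + 11.628/1.25) × 10.507 = 157.3, so 158/197.
- SDs exchanged between arms: (11.628 + 5.664/1.25) × 10.507 = 169.8, so 170/213, or 171/214 with a t correction.

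The stated 172/214 therefore reproduces to within two patients, but with the SDs exchanged. Both assignments are carried forward.

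**Step 2: dilution under intention to treat.** Let p be the share of the open access arm that declines and behaves like controls. The expected difference is (1 − p)δ, and

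power = Φ((1 − p)δ/SE − 1.96), with 90% power lost at p = 1 − 3.2415 × SE/δ.

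At 225/275 with SDs as labelled, SE = √(5.664/225 + 11.628/275) = √0.06746 = 0.2597, so the crossing is at 1 − 0.842 = 15.8%. With SDs exchanged, SE = √(11.628/225 + 5.664/275) = 0.2689, and the crossing is at 12.9%.

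The open access variance may also be treated as a mixture, p·SD_std² + (1 − p)·SD_open² + p(1 − p)δ². All four variants, with 500 analysed:

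| SDs, variance | 0% | 10% | 20% | 30% | 90% lost at |
|---|---|---|---|---|---|
| labelled, fixed | 97.1% | 93.4% | 86.9% | 76.9% | 15.8% |
| labelled, mixture | 97.1% | 94.0% | 88.7% | 80.4% | 17.9% |
| exchanged, fixed | 96.1% | 91.7% | 84.5% | 74.0% | 12.9% |
| exchanged, mixture | 96.1% | 90.8% | 82.1% | 69.9% | 11.2% |

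A check that does not depend on the SDs: if 386 gives exactly 90%, then 500 at the same ratio tolerates 1 − √(386/500) = 12.1% declining.

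At the minimum 172/214 the four crossings are 4.2%, 4.9%, 0.6% and 0.5%, so there is almost no margin.

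**Step 3: what the loss wording implies.** If decliners really vanished, δ would stay at 1 and only the open access n would fall, to 275(1 − p). With SDs as labelled, power is 96.1%, 94.7%, 92.8% and 89.9% at 10, 20, 30 and 40% declining. The same 500 patients would hold about 90% up to roughly 40% declining, against roughly 11–18% under intention to treat.

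**Step 4: what the unequal ratio buys.** At 250/250, SE = √(17.293/250) = 0.2630. With SDs as labelled, 225/275 gives 0.2597, a fall of 1.2%. With SDs exchanged it gives 0.2689, a rise of 2.2%. Neither matters against a difference reduced by 10–30%.

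**The case against.** The best defence has four parts.

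*No shortfall is shown.* The article gives no decline rate. At 10% declining, 500 patients still give about 91–94%. Raising the total is a legitimate answer to dilution, and the Discussion names it beside the unequal ratio. This stands: a reader might infer that the trial is underpowered, and the document does not support that.

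*One contact may already be the diluted difference.* The Sample size section speaks of a difference between the groups, which could mean the randomised groups. On that reading power holds. It cannot be excluded, but the text does not say so, and the separate allowance for decliners suggests that the effect and the refusals were thought of apart.

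*The intention-to-treat sentence is clear, and the loss wording may refer to other analyses.* Decliners may fail to return the 18-month questionnaire, and in a per-protocol analysis extra patients do replace refusers. So the article does not commit to dropping decliners from the primary analysis, and it would be wrong to say that it does. The stated 90% power, however, is for the number of contacts, and a per-protocol analysis does not restore the power of the intention-to-treat one.

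*Two further criticisms fail.* A reader might call the ten per cent figure an error, since 0.55/0.45 is 22% more. But 275 is 10% above an equal split of 250, and 55 against 45 is ten percentage points, so the wording is ambiguous rather than wrong. A reader might also count silent patients as further dilution, because the Ethics section says: "If lack of response the patient is reallocated into standard telePRO with a red status and a clinician will contact the patient". That happens only after twice the fixed interval. For a 12-month interval this is 24 months, beyond the 18-month follow-up; for 3- and 6-month intervals it is 6 and 12 months at the earliest. The safety net is also part of open access as described, so its use is not simply crossover.

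**Conclusion.** The point holds in a conditional form. The article plans for decliners as losses to be replaced, while its own analysis rule and outcome source keep them in the open access arm on control care. The power statement makes no visible allowance for the resulting (1 − p) × effect.

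With 500 analysed, the stated 90% is kept only while fewer than roughly 11–18% decline (about 16% with SDs as labelled), and beyond that power falls gradually. The loss wording makes the design look robust to about 40%.

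This rests on four assumptions: one contact is the effect in acceptors, decliners behave like controls, all 500 are analysed, and the test is two-sided. Other attrition would lower the threshold. The planned intention-to-treat comparison stays valid, so this is a correction worth making before outcome data are seen and not a flaw that undermines the trial.

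**What to change.** 1. State that patients who decline, and those moved back to standard telePRO by the safety net, stay in the open access arm for the primary intention-to-treat analysis and are still sent the 18-month questionnaire.
2. Stop describing decliners as loss to follow-up. Keep that term for patients whose outcome is not observed.
3. Give the expected decline share, and say whether the one-contact difference is the intention-to-treat effect or the effect in acceptors.
4. Restate intention-to-treat power on (1 − p) × effect over a range of decline shares, naming the SD used for each arm.

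The cost is a few sentences and one small table. No extra enrolment is asked for. The only drawback is that the stated power may look less favourable.

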### Study timeline

Inclusion and randomisation with baseline assessments will take place from January 2016. Follow-up assessment will take place 18 months after randomisation. Baseline and follow-up assessments are shown in Table 1. Figure 4 presents the inclusion of patients and the stages in the study.

**Table 1 Tab1:** Primary and secondary outcomes, data sources, and timeline for measurements

Outcomes	Data sources	Measurement/month
Resource utilisation		
1. Number of contacts	The Hospital Business Intelligence Register, Central Denmark Region	0–18
Quality of care		
2. Well-being	WHO-Five Well-being Index (WHO-5)	0, 18
3. General health	Item from The Short Form Health Survey (SF-36)	0, 18
4. Mortality	The Hospital Business Intelligence Register, Central Denmark Region	0–18
5. Number of seizures	Item from the epilepsy questionnaire, Central Denmark Region	0, 18
6. Treatment side effects	Item from the epilepsy questionnaire, Central Denmark Region	0, 18
Patient perspective ^a^		
7. Health literacy	The Health Literacy Questionnaire (HLQ) sub scale 4, 6 and 9	0, 18
8. Self-efficacy	General Self-Efficacy scale (GSE)	0, 18
9. Patient activation	Items from Patient Activation Measure (PAM)	0, 18
10. Confidence, safety, and satisfaction	Items from a PREM questionnaire, Danish Cancer Society	0, 18

^a^ The patient perspective is primarily explored by qualitative methods in a complementary PhD study

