*AmbuFlex* is a generic clinical PRO system which is not limited to specific patient groups, organisations or medical record systems [12]. As of December 2015, AmbuFlex had been implemented in nine patient groups at 15 outpatient clinics in Denmark [13]. An analysis initiated by the Danish government based on experiences with AmbuFlex has demonstrated a positive national business case and considerable quality gain [14]. The Danish government and Danish regions, who run the public hospitals, have decided on an agreement for nationwide implementation of PRO in three diagnostic group, including epilepsy, before 2020. AmbuFlex was implemented for epilepsy outpatients at Aarhus University Hospital in March 2012 and is now used at three neurological departments in the Central Denmark Region. As of August 2016, 4,513 epilepsy outpatients have been referred to AmbuFlex, which are about two-thirds of all epilepsy outpatients in the region. The PRO questionnaire used contains information on specific aspects of daily life with epilepsy and has been developed in close cooperation with clinicians and patients. Face validity is fundamental and has been ensured during the development of the questionnaire [12, 13]. A graphical PRO overview is presented to the clinicians, who use the PRO data for clinical decisions together with other available clinical data in the record to decide whether the patient needs a visit or not. If a PRO questionnaire is used to evaluate the patient’s need for a hospital visit, the PRO data must be obtained outside the hospital. This is called tele-patient-reported outcome (telePRO) [12]. Experiences from epilepsy outpatient clinics have shown that of 8,256 PRO-based contacts, 48% were handled without additional contact to the patient other than the PRO questionnaire [13]. A preliminary interview study has indicated that patients experience greater flexibility in care, the saving of time, improved communication with the clinicians, and increased knowledge about their own disease [13, 15].

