### Intervention

#### Reference group – standard telePRO

AmbuFlex (standard telePRO) is used in three epilepsy outpatient clinics in Central Denmark Region. In standard telePRO, outpatient follow-up activity is determined by a clinician and patients receive a questionnaire at fixed intervals (3, 6, or 12 months). The questionnaire includes information about aspect of daily life with epilepsy such as seizures, symptoms, medication adherence, and social aspects. Responses are automatically processed according to a specific algorithm and given a “green”, “yellow”, or “red” status. A red status indicates that the patient needs or wishes contact with the clinic, a green status that the patient has no current need of attention, while a yellow status indicates that the patient may need to be seen in the clinic, but a clinician has to decide whether further contact is needed. The patient can always overrule a decision by requesting contact. They can choose two different contact forms in the questionnaire: telephone consultation or a face-to-face consultation at the clinic. Non-responders get three reminders and are contacted if do not respond. Clinicians keep track of incoming yellow and red responses, and non-responders, and this information is presented on a PRO alert list. The PRO overview (Fig. 1) is presented graphically to the clinician within the electronic health record system, and used as decision aid together with other available health record information to decide whether the patient needs a visit or not [13].

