### Primary outcome

#### Resource utilisation

Number of contacts includes all contacts with the outpatient clinic in the study follow-up period, including face-to-face consultations with a physician, face-to-face consultations with a nurse, and telephone consultations. In addition, other health care contacts will be gathered, e.g., epilepsy-related emergency room visits and hospitalisations as well as hospitalisation related to co-morbidity. Data will be gathered from the Hospital Business Intelligence Register in Central Denmark Region.

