Another potential challenge may be how individuals in the intervention group will use the “My Epilepsy” website. Some patients are better able to decide themselves when they need to contact the clinic, while others are more reserved and afraid to be a nuisance. Several patients that have used standard telePRO have pointed out the benefit of getting a fixed questionnaire once a year. They do not believe they would remember to answer if they had to do it on their own. This could signify that even though they may not feel the need for a clinical appointment, but do feel a form of security in answering the fixed interval questionnaire. This will be taken into consideration in the study, since all patients in the intervention group will receive a questionnaire if they do not respond within two times the referred interval, for example, within 24 months if they are assigned a 12-month questionnaire interval. Another concern could be that patients in the open access group could choose to make a call instead of answering the questionnaire when they need to get in contact with the clinic. If they behave in this way, the benefit of using PRO in clinical practice will be reduced.

Standard telePRO has been well integrated into clinical practice in three epilepsy clinics in Central Denmark Region since 2012. A new patient-initiated approach has been developed that may result in potential benefits in terms of the patient perspective and resource utilisation. The potential benefits as well as possible drawbacks need to be evaluated. We have decided to combine qualitative and quantitative research methods in two parallel PhD studies. The intention of the complementary qualitative PhD study is to further explain the findings from the randomised study by providing a description of the various ways in which telePRO is manifested and an interpretation of the underlying mechanisms of action. The two studies will complement each other and contribute with important research-based knowledge to guide future telePRO interventions in relation to effect on resource utilisation, quality of care, and the patient perspective.

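### The 18-month contact count closes before the 24-month safety-net contact of silent 12-month-interval open access patients, so in that stratum postponed contacts are scored as avoided

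*Protocol article*

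**What the plan says.** The Study timeline section of the protocol article states: "Follow-up assessment will take place 18 months after randomisation". Table 1 gives the measurement period for number of contacts as months 0–18, and the Primary outcome section defines the endpoint over that period: "Number of contacts includes all contacts with the outpatient clinic in the study follow-up period".

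Standard telePRO patients receive a questionnaire every 3, 6 or 12 months. In the open access arm the patient decides when to respond, subject to a safety net: "patients have to answer the questionnaire before twice the fixed interval has elapsed". The description of the website gives the 12-month case as its example: "if the patient is referred with a 12-month interval, the patient has to respond within two years". The Discussion repeats it: "within 24 months if they are assigned a 12-month questionnaire interval". A patient who does not respond in that time is sent a questionnaire, given red status and contacted by a clinician. The Ethics section adds that such a patient is moved back to standard telePRO.

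Nowhere does the article extend the count past month 18, include a safety-net contact still pending then, or separate the primary comparison by interval. The first hypothesis under Objectives is that open access has fewer contacts.

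**The concern.** Twice a 12-month interval is longer than the counting window. A 12-month open access patient who stays silent finishes the primary count with no contacts while one compulsory contact is still due. The same patient in the standard arm always has one scheduled questionnaire, at month 12, inside the window. The 18-month total cannot tell a contact that was avoided from one that was moved past the cut-off, and the ambiguity runs in the direction of hypothesis 1. At stake is whether a lower count in open access can be read as reduced resource use.

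**Working it through.** The plan gives no figure of its own on this point, so the check counts scheduled events to months 18 and 24.

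**Inputs from the protocol article**
- Count window: months 0–18 (Study timeline, Table 1).
- Standard interval i = 3, 6 or 12 months (Reference group).
- Safety net at 2i = 6, 12 or 24 months (website description, Discussion).
- After the safety net: red status, clinician contact, return to standard telePRO (Ethics).
- Month 0: both arms receive the fixed PRO questionnaire with the baseline questionnaire (Randomisation).
- Contact rate per standard questionnaire, from the Background: "of 8,256 PRO-based contacts, 48% were handled without additional contact to the patient other than the PRO questionnaire". Hence p = 1 − 0.48 = 0.52.
- Planned difference: one contact (Sample size).

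**Assumptions**
- The open access patient never self-initiates.
- Each safety-net event yields one recorded contact.
- p is the same for all intervals.
- The fixed interval restarts at the safety-net date.
- Events due exactly at the cut-off count.

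**Formulas, contacts by month T**
- Standard: p × (number of whole intervals in T).
- Open access, silent: 0 if T < 2i; otherwise 1 + p × (number of whole intervals in T − 2i).

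| Interval | Standard, 18 m | Open, 18 m | Gap | Standard, 24 m | Open, 24 m | Gap |
|---|---|---|---|---|---|---|
| 3 m | 6 × 0.52 = 3.12 | 1 + 4 × 0.52 = 3.08 | 0.04 | 8 × 0.52 = 4.16 | 1 + 6 × 0.52 = 4.12 | 0.04 |
| 6 m | 3 × 0.52 = 1.56 | 1 + 1 × 0.52 = 1.52 | 0.04 | 4 × 0.52 = 2.08 | 1 + 2 × 0.52 = 2.04 | 0.04 |
| 12 m | 1 × 0.52 = 0.52 | 0 | 0.52 | 2 × 0.52 = 1.04 | 1 | 0.04 |

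Only the 12-month row changes with the window: 0.52 − 0.04 = 0.48 of its 18-month gap comes from where the count is cut.

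**Dependence on p.** For 12-month patients the gap is p at 18 months and 2p − 1 at 24 months. The window therefore contributes 1 − p whatever p is. If p were below 0.5, the sign would change: at an assumed p = 0.40, open access shows 0.40 fewer contacts at 18 months (0.40 vs 0) but 0.20 more at 24 months (0.80 vs 1).

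**Overall size.** Let s be the share on a 12-month interval and q the share of those who stay silent to month 18. Neither is given; each is taken as 0.25 to 1.
- 18 months: 0.52 × s × q. This is 0.0325 at s = q = 0.25, 0.13 at 0.5, and 0.52 at 1.
- 24 months: 0.04 × s × q, from 0.0025 to 0.04.

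**Upper bound with everyone silent.** The mean 18-month gap is 0.52s + 0.04(1 − s). Three assumed mixes of 3/6/12-month intervals:
- 20/30/50%: 0.28 of 1.352 standard contacts (21%).
- 10/30/60%: 0.328 of 1.092 (30%).
- 5/25/70%: 0.376 of 0.91 (41%).

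**The case against.** Longer spacing is part of the intervention, and contacts over 18 months is an openly defined outcome, so fewer contacts in that period are real for that period. That stands as a description of 18 months. It does not carry over to a general claim of reduced resource use, because over a full safety-net cycle the schedule-only gap falls from 0.52 to 0.04.

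The standard arm's month-24 questionnaire is cut off as well. True, but on the assumed rate it yields a contact about half the time, whereas the safety net always triggers one.

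The figures are upper bounds. Self-initiation is the point of the intervention, patients may telephone, and those who decline stay on standard telePRO but are analysed as randomised. The 52% comes from all intervals, not from annual patients. All of this stands, and it is why only a range can be given.

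A reader might infer three stronger things that the document does not support:
- **That 6-month patients lose a second compulsory cycle at month 24.** The Ethics section returns non-responders to standard telePRO after the safety net, so there is no second cycle and the 18-month gap is about 0.04.
- **That the count starts too early and so favours open access.** The protocol says "Intervention participants will receive detailed information about the open access approach two weeks after" the clinician's response to the fixed PRO. Contacts prompted by that PRO arise in both randomised arms before they differ. They add noise and dilute the relative effect, but do not bias the difference.
- **That the safety net goes unobserved.** For 3- and 6-month patients it falls at months 6 and 12, inside the window. Only the 12-month safety net lies outside it.

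**Conclusion.** The concern holds for open access patients on a 12-month interval who make no contact before month 18. For them the schedule alone produces about 0.52 vs 0 contacts at 18 months and about 1.04 vs 1 at 24 months, so postponement is scored as avoidance, in favour of hypothesis 1. The 3- and 6-month strata are essentially unaffected.

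The contribution to the overall difference is about 0.03 to 0.52 contacts per patient over the assumed shares, against the planned difference of 1. It could be trivial or about half the planned effect. The document does not support saying that any observed saving would be wholly an artefact. The figures rest on the 52% rate applying to 12-month patients and on each safety-net event being recorded as one contact. The existence and direction of the artefact rest only on 24 months being later than 18 and on some 12-month controls having a contact after their month-12 questionnaire. The length of the safety-net interval is a clinical matter and is not judged here.

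**What to change.** Extend the register count for the primary outcome to month 24 and include later contacts that arise from questionnaires or safety-net events due by month 24, by the same rule in both arms. Tying closure to due events lets month-24 events be handled without bringing in contacts from the next cycle. Keep randomisation as the start of the count and keep the patient-reported outcomes at 18 months.

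Cost: a protocol amendment, one later extraction from the same register, and a rule linking contacts to due events. No visits or patients are added. The drawback is a primary readout at least six months later.

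If the 18-month count stays primary:
- Report it by assigned interval.
- Add a sensitivity analysis that counts the pending safety-net contact of silent 12-month open access patients. Counted alone, it gives 0.52 vs 1 and so bounds the result from the other side. Also crediting controls with their month-24 questionnaire at the assumed rate gives 1.04 vs 1.
- Describe fewer contacts as avoided or deferred, and do not claim reduced resource use from the 18-month count alone.
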